## Abstract

**Background:**

Familial adenomatous polyposis (FAP) is a rare autosomal dominant disease characterized by germline mutations in the *Adenomatous Polyposis Coli* (*APC)* gene, resulting in the development of numerous colorectal adenomas. As these patients have a high risk of developing colorectal cancer (CRC), guidelines suggest prophylactic colectomy during early adulthood, however, adenoma development is still observed in the remaining intestinal tract. Therefore, FAP patients would benefit from chemoprevention strategies reducing the development of adenomas. Recent work in mice reveals a chemopreventive effect of lithium on the development of adenomas by inhibiting the expansion of *Apc* mutated intestinal stem cells (ISCs) within the crypts of normal intestinal mucosa. Here, we aim to investigate the effect of lithium on the spread of *APC* mutant cells within the human intestinal epithelium.

**Methods:**

This prospective phase II single arm trial has a duration of 18 months. FAP patients (18–35 years) with a genetically confirmed *APC* mutation who did not undergo colectomy will be treated with lithium carbonate orally achieving a serum level of 0.2–0.4 mmol/l between month 6 and 12. Colonoscopy with biopsies of normal intestinal mucosa will be performed at baseline and every six months. The primary endpoint is the effect of lithium on the spread of *APC* mutant cells within intestinal crypts over time by using *APC* specific marker *NOTUM *in situ hybridization. Secondary endpoints include change in adenoma burden, patient reported side effects and safety-outcomes. Total sample size is 12 patients and recruitment will take place in the Amsterdam UMC, location AMC in the Netherlands.

**Discussion:**

The outcome of this study will function as a proof-of-concept for the development of novel chemoprevention approaches that interfere with the competition between normal and mutant ISCs.

*Trial registration*: ClinicalTrials.gov (https://clinicaltrials.gov/): NCT05402891 (June 1, 2022) and the EU Clinical Trials Register: EuraCT 2022-000240-30 (January 1, 2022).

**Supplementary Information:**

The online version contains supplementary material available at 10.1186/s12876-022-02442-3.

## Background

Familial adenomatous polyposis (FAP) is an autosomal dominant disorder with a germline mutation in a tumor suppressor gene, *Adenomatous Polyposis Coli* (*APC*) [1]. FAP is a rare condition with an estimated prevalence of 1 out of 5.000–7.000 births [2]. Although FAP is a hereditary disease, it may also be caused by a de novo mutation in the *APC* gene, responsible for approximately 25% of cases [3]. Classical FAP is characterized by the early onset of hundreds to thousands of adenomas in the colon and rectum, and if left untreated, the risk of developing colorectal cancer (CRC) is nearly 100%, occurring between the age of 35 and 45 [2, 4]. To prevent CRC, guidelines suggest prophylactic surgery in these patients dependent on adenoma burden, personal preference and family history [5]. These surgeries are mostly performed around the age of 20, and come with complications and postoperative morbidity [6, 7]. After surgery, new adenomas will develop not only in the remaining parts of the colorectum but in case of pouch creation also in the terminal ileum, in which previously no adenomas were detected, resulting in an ongoing risk of developing intestinal cancer in these patients [8, 9]. Therefore, these patients need lifelong endoscopic surveillance, and potential endoscopic and surgical interventions to prevent intestinal cancer [8, 9]. Patients with FAP would greatly benefit from chemo-preventive strategies that aim to prevent adenoma formation, ultimately resulting in postponing or even avoiding prophylactic surgery. Up to date, several studies on chemo-preventive therapies for patients with FAP were conducted. Due to lack of a significant effect and the adverse events (AE’s) in these patients, no chemo-preventive therapy is routinely used in clinical practice [10–12]. Recent translational work elucidated the molecular mechanism of early oncogenic transformation in FAP and revealed a potential chemopreventive effect of lithium on adenoma development [13, 14]. In the next sections, we will elaborate on this molecular mechanism and potential chemopreventive therapy with lithium.

### *APC*-mutant cells act as supercompetitors

In FAP, intestinal tumor development is initiated by the loss of the second wild type *APC* allele [15]. The APC protein is a critical negative regulator of the Wnt signaling pathway, an essential signaling route involved in the maintenance of intestinal stem cells (ISCs) which are located in the crypt bottom [16]. Loss of *APC* function results in unrestrained activation of the Wnt signaling cascade which can lead to the development of premalignant adenomas [16]. Previous work demonstrated that ISCs that have acquired an *Apc* mutation have a competitive benefit over wild type (WT) ISCs [15]. As a result, *Apc*-mutant cells gradually replace all WT ISCs, resulting in permanent fixation of a mutation in the crypt bottom and initiation of adenoma formation [13]. Critically, recent studies by us and others have now revealed that *Apc*-mutant ISCs in fact act as supercompetitors, that actively disadvantage WT ISCs [13, 14]. This competitive advantage is due to the expression of Wnt antagonists (e.g. NOTUM, WIF1, DKK2) by *APC*-mutants to which they themselves are insensitive, but result in active differentiation of WT ISCs that are heavily dependent on Wnt signaling (Fig. 1).

**Fig. 1 Fig1:**
[figure not shown]
Crypt fixation and chemoprevention with lithium treatment. *APC* = *adenomatous polyposis coli* tumor-suppressor gene. DKK2 = Dickkopf WNT Signaling Pathway Inhibitor 2. ISCs = intestinal stem cells. WIF1 = WNT Inhibitory Factor 1. ISCs reside at the bottom of the crypts of the epithelium of the colon where they engage in ongoing neutral competition with each other for a position in the crypt. These neutral dynamics are disturbed whenever an ISCs acquires a second mutation in the *APC* allele. *APC*-mutant ISCs have a competitive advantage by secreting Wnt antagonists (e.g. NOTUM, WIF1, DKK2) that drive the differentiation of WT ISCs, thereby resulting in mutant crypt fixation and the development of premalignant adenomas. In this study, we propose that boosting the Wnt pathway in WT ISCs using lithium diminishes this competitive advantage and prevents adenoma formation. This figure was created by using Adobe Illustrator 2022 (version 26.0.3)

### Lithium as chemopreventive therapy

The mechanism by which *APC*-mutant cells outcompete their wild type counterparts immediately suggests a putative target for chemoprevention. Rendering WT ISCs insensitive to the secreted Wnt antagonists by *APC*-mutant cells could prevent further expansion of *APC*-mutant clones. In order to counteract these Wnt antagonists, we proposed to boost the Wnt pathway in WT ISCs using GSK-3β inhibitor lithium, and observed a marked decrease in crypt fixation which consequently resulted in a reduced adenoma burden in a mouse model of FAP [13]. This study implemented a novel way of tracing *Apc-*mutant cells by labeling these cells for Wnt antagonist *Notum*, and analyzing their spread through the crypts over time [13, 14]. In this study in mice, a reduction in the expansion of *Notum* positive clones was observed using a low dose lithium administration (using lithium serum levels of 0.2 mM) [13]. In addition, our work and other studies reveal that *NOTUM* is also highly expressed in crypts and adenomas from FAP patients (Fig. 2) [13, 14, 17]. Until now, no data on lithium use in patients with FAP is available. However, several studies on long term lithium use in patients with bipolar disorders demonstrated a reduced incidence on CRC and cancer in general [18, 19]. Therefore, we propose to trace the spread of *APC*-mutant cells using a similar strategy to assess the effect of low-dose lithium on stem cell competition and number of adenomas in FAP patients.

**Fig. 2 Fig2:**
[figure not shown]
*NOTUM* in situ hybridization (ISH) in human FAP adenomatous lesion. Fluorescent staining of human intestinal adenomas was visualized with a SP8X confocal microscope using Leica Application Suite software (version 3.5.7)

## Objectives

### Primary objective

The primary objective of this study is to evaluate the effect of low-dose lithium on the spread of *APC*-mutant cells within intestinal crypts of FAP patients over time. This will be assessed by using an *APC* mutation specific marker (*NOTUM*) and is defined as a significant reduction of fixed crypts and reduction of fixed clone size by 50%.

### Secondary objectives

To evaluate:The effect of low-dose lithium on number of adenomas and size, determined as sum of diameter of all adenomas;Side effects of low-dose lithium in FAP patients, evaluated by lithium side effects questionnaires;The safety of low-dose lithium in FAP patients, evaluated by adverse events, findings during physical examination and laboratory tests.

## Methods

### Study design

The CHAMP-study is a single arm, phase II trial conducted in the Amsterdam UMC, location AMC (AMC) in the Netherlands. The duration of this study will be 18 months in which lithium will be administered between month 6 and 12. The study has been approved by the Medical Ethical Committee of the Amsterdam UMC, location AMC, and has been registered in ClinicalTrials.gov (NCT05402891). This protocol was designed following the Standard Protocol Items: Recommendations for Interventional Trials (SPIRIT). A flowchart of the study design is shown in Fig. 3.

**Fig. 3 Fig3:**
[figure not shown]
Flowchart of the study design (as of May 2, 2022). ^1^Hematology: haemoglobin, thrombocytes, leukocytes. ^2^Chemistry: GFR, creatinine, urea, sodium, potassium, calcium and TSH (if deviating T4). ^3^A pregnancy test is required for participants with the female gender. ^4^Urine sample: urine osmolality and urine creatinine. This figure was created by using Adobe Illustrator 2022 (version 26.0.3)

### Study population

Patients diagnosed with FAP, between the age of 18 and 35, with intact colons/rectums, are eligible for this study. No exclusion will be made based on sex or race. For this study no control group will be included, but patients serve as their own control in the non-treatment phase.

### Inclusion criteria

Patients must meet all of the following criteria for inclusion in the study:Age between 18 and 35 years;Confirmed *APC* germline mutation and one of the following:Minimum of 100 colorectal adenomas;Minimum of 50 colorectal adenomas and a positive family history of a classical FAP phenotype (> 100 colorectal adenomas);Intact colon;Participant is willing and able to give informed consent for participation.

### Exclusion critera

Patients that meet any of the following criteria will be excluded from participation in this study:Participation in any other clinical intervention study; observational trials accepted;Lithium use prior to participation of the study;Pregnancy, breast-feeding or no use of anticonception;No normal intestinal mucosa left for normal tissue biopsy;Indication for colectomy within 2 years;Known renal impairment, defined as GFR < 60 ml/min;Known severe cardiac disorder;Known severe brain injury;Hypothyroidism;Hyponatremia, defined as sodium < 130 mmol/L;Positive family history of Brugada syndrome;Co-medication known for interacting with lithium;Regular non-steroidal anti-inflammatory drug (NSAID) use (defined as more than twice a week for 4 consecutive weeks) within 3 months prior to baseline;Use of immunosuppressive or anti-inflammatory drugs within 3 months prior to baseline;Use of any other FAP directed drug therapy within 3 months prior to baseline (use of any alternative supplements e.g. turmeric or fish-oil must be noted in patient diary).

### Intervention

Lithium carbonate will be administered by an oral tablet once a day for six months. Subjects will be treated with a starting dose of 200 mg, which will be increased to 300 mg after 5 days. To limit AE’s and side-effects, the lowest effective dose will be administered. The target serum level of lithium is 0.20–0.40 mmol/L and this will be maintained by regular testing of lithium serum levels and dose adjustments if required.

### Outcome measures

#### Primary outcome

The spread of *APC*-mutant cells within intestinal crypts of FAP patients over time will be assessed by quantifying clone sizes as proportions of the crypt circumference positive for *NOTUM* (in parts of eight, 1:8 to 8:8). When a whole crypt is positive for *NOTUM* (8:8), this crypt is fixed (crypt fixation) [12].

#### Secondary outcomes

Secondary endpoints include:Difference in number and size of adenomas, determined as sum of diameter of all adenomas between baseline and end of study;Patient reported side-effects of low-dose lithium in FAP patients, using a lithium side effect questionnaire (Additional file 1: Lithium side effect questionnaire);Safety outcomes of low-dose lithium by analyzing adverse events, physical examination and laboratory findings including hemoglobin, thrombocytes, leukocytes, GFR, creatinine, urea, sodium, potassium, calcium TSH (if deviating T4), urine osmolality and creatinine.

Given the fact that dietary factors can influence intestinal stem cell dynamics, we also aim to monitor the following parameters: number of cups of coffee per day (decaffeinated coffee not included); turmeric use (gram per day); number of fish oil capsules per day (amount of eicosapentaenoic acid in terms of mg) and history of smoking (if yes number of pack years).

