### Recruitment, study procedures and assessments

Participants will be recruited from the large cohort of FAP patients at the hereditary GI Cancer clinic at the Amsterdam UMC. Prior to their routine surveillance colonoscopy, patients will be invited to participate by a member of the study team. In total 12 patients will be included in this trial. For all patients, lithium will be administered for a period of six months, between month 6 and 12. Since every participant is given the same treatment, no randomization will take place.

During the course of the study, four colonoscopies (at t = 0 months, t = 6 months, t = 12 months, t = 18 months) will be performed to evaluate the effect of lithium on clone sizes and stem cell dynamics in mucosal biopsies and total adenoma burden. Physical examination (including vital signs) will be performed at baseline and every six months, at time of endoscopy. Laboratory testing will be performed at baseline and every two months from start of lithium treatment. Serum lithium levels will be measured at day 12 and day 22 after start of treatment. When the therapeutic range is reached, serum levels will be measured once a month. Blood samples for determining serum levels must be collected 12 h after oral administration of lithium. If necessary, dose adjustments will be made by the investigator based on serum levels, laboratory tests and side effects. Serum lithium levels will be monitored 12 days after dose adjustments, until the therapeutic range is reached or side-effects diminished. Further check-ups will be performed through telephone interviews to evaluate AE’s and side effects using a lithium side effect questionnaire base on a previously designed tool [20]. A schedule of activities is included in the supplementary materials (Additional file 2: Schedule of activites). More detailed information on study visits, follow-up, data monitoring, safety reporting and auditing is included in the study protocol and clinical trial registry records [21].

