#### Assessment of adenoma burden

A full colonoscopy will be performed at baseline, and at months 6, 12 and 18 to assess adenoma burden and to take biopsies. During colonoscopy, Boston Bowel Preparation Scale (BBPS) should be 2 for each segment and cecal intubation achieved. Adenoma burden will be assessed by estimating the number and size (estimated using a biopsy forceps) of adenomas in each of the 6 colorectal segments: cecum, ascending colon, transverse colon, descending colon, sigmoid and rectum (including retroflexion). For each colonoscopy, the table below will be used to calculate the sum of diameter of adenomas to determine the total colorectal adenoma burden (Table 1). Standard white light endoscopy (WLE) will be used; Narrow band imaging (NBI) is used at the discretion of the endoscopist. Adenomas ≥ 5 mm should be excised at all colonoscopies. At each endoscopy, also two random biopsies of normal mucosa will be taken in each segment, resulting in a total of 12 biopsies of normal intestinal mucosa. Video recordings will be made for all colonoscopies (only using WLE). All four videos of each participant will be reviewed by two separate independent expert endoscopists in a random order, assessing the adenoma burden using the table below. If there is a disagreement of more than 30% in the adenoma burden assessment between the two reviewers, a third independent reviewer will be engaged. Then, the average of these three reviewers will be used for further analysis.

**Table 1 Tab1:** Total adenoma burden

Segment	Number of adenomas			
	1–2 mm	3–5 mm	6–10 mm	> 10 mm
Cecum				
Ascending colon				
Transverse colon				
Descending colon				
Sigmoid				
Rectum				
Total adenoma burden				

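### The secondary adenoma endpoint runs from baseline to month 18, pooling 12 untreated months with 6 treated ones, so it cannot by itself show the effect of lithium

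*Protocol article*

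**What the plan says.** All references are to the protocol article.

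- **Objective** (Secondary objectives): to evaluate "The effect of low-dose lithium on number of adenomas and size, determined as sum of diameter of all adenomas".
- **Endpoint** (Secondary outcomes): "Difference in number and size of adenomas, determined as sum of diameter of all adenomas between baseline and end of study".
- **Timeline** (Study design): "The duration of this study will be 18 months in which lithium will be administered between month 6 and 12".
- **Control** (Study population): "For this study no control group will be included, but patients serve as their own control in the non-treatment phase".
- **Measurements**: "A full colonoscopy will be performed at baseline, and at months 6, 12 and 18 to assess adenoma burden and to take biopsies" (Assessment of adenoma burden). The same section has adenomas of 5 mm or more removed at each of these colonoscopies, and all four videos read independently in random order.
- **Analysis** (Data analysis): secondary outcomes are described over follow-up, without a test.

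The article does not spell out that the end of study is month 18. The 18-month duration and the last colonoscopy at month 18 leave no other reasonable reading.

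**The concern.** The objective asks what lithium does to adenoma number and size. The only comparator in the design is each patient's own time off drug. The defined endpoint subtracts the first measurement from the last, so both untreated periods are added to the treated one instead of being set against it. For clone size, the section Assessment of size of fixed clones compares the periods preceding, on and following lithium. The adenoma endpoint comes from the same four colonoscopies but is not defined that way.

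Adenoma number and size are the trial's only efficacy measure at the level of visible lesions. If the reported result is the month 0 to 18 difference, a fall could reflect excision or natural course, and a rise could hide a real slowing on drug. Neither could be attributed to lithium or used to exclude an effect.

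**Working it through.** The article gives no numerical target or power for this endpoint, so there is no figure of its own to reproduce. The 12 patients and the 50% reduction under Sample size calculation concern the fitness of mutant cells.

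**1. Timeline** (inputs: lithium from month 6 to month 12; duration 18 months)

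- Treated: 12 − 6 = 6 months, or 6/18 = 33.3% of the window.
- Untreated: 18 − 6 = 12 months, or 12/18 = 66.7%.
- Off-drug tail: 18 − 12 = 6 months.

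**2. What the single difference identifies.** Let u be the change in an untreated six months (assumed equal in both untreated periods) and t the change in the treated six months. The endpoint is u + t + u = 2u + t. A change of 27 units (illustrative) fits all of these:

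| u | t | 2u + t | Reduction on drug, 1 − t/u |
|---|---|---|---|
| 9 | 9 | 27 | 0% |
| 10.8 | 5.4 | 27 | 50% |
| 13.5 | 0 | 27 | 100% |

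One equation in two unknowns cannot tell no effect from complete suppression.

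**3. Dilution.** Assume constant untreated growth u, an on-drug reduction r in growth, an immediate effect, and no carry-over or rebound. Then t = (1 − r)u. The 0–18 change is (3 − r)u against 3u without drug, a relative reduction of r/3. The 6–12 change against the 0–6 change shows r in full.

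| r | Seen in months 0–18 | Seen in 6–12 against 0–6 |
|---|---|---|
| 25% | 8.3% | 25% |
| 50% | 16.7% | 50% |
| 100% | 33.3% | 100% |

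The middle column also needs the 3u expected without drug, which the endpoint does not supply.

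**4. Relaxing the timing assumption**

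- *Delayed effect.* If a benefit of 0.5u falls entirely in months 12–18, the 6–12 contrast is u against u, or 0%. The 12–18 change is 0.5u, and the 0–18 change is 2.5u against 3u, still 16.7%.
- *Full rebound.* If the 12–18 change is (1 + r)u, the total is u + (1 − r)u + (1 + r)u = 3u. The 0–18 change shows 0%, while 6–12 against 0–6 still shows r.

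So neither contrast is enough alone, and months 12–18 must be shown separately.

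**5. Excision.** Suppose burden is scored before excision at each visit (assumption). Let S, s and s′ be the burden removed at months 0, 6 and 12, and let growth be g per interval with no drug effect.

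- Months 0–18: 3g − (S + s + s′), which can be negative with an inert drug.
- Raw 0–6 change: g − S. Raw 6–12 change: g − s. Their difference is (g − s) − (g − S) = S − s. If the first clearance removes more than the second (S > s), this is positive and biased against lithium.
- Starting each interval from the burden left after excision: both changes are g and the difference is 0.

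The period contrast therefore works only if removed lesions are accounted for.

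**The case against.** The strongest reply is that one condensed sentence is being read too hard. Burden is scored at all four colonoscopies, the section Recruitment, study procedures and assessments says these serve to evaluate lithium's effect on burden, and Data analysis provides for describing secondary changes over follow-up. A reader might infer that the plan ignores months 6 and 12, or has no control for adenomas at all. The documents do not support that: the data will exist and interval summaries are permitted. What remains is that the endpoint as defined names a different contrast, and the general wording elsewhere does not replace it. This is a stated contrast that does not fit its objective, not a detail left to a fuller document.

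A second reply concerns timing. The Discussion says lithium is meant to act on stem cells before crypts become fixed, and adenomas follow fixation, so the effect on visible lesions may lag. This stands, and it is why months 12–18 need their own report. It does not rescue the pooled difference, which mixes any late effect with the untreated run-in.

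A reader might also infer that moving to months 6–12 raises the visible effect from 17% to 50%. That holds only for one assumed effect size under constant growth with no lag. The article's 50% refers to clone size, crypt fixation and clone fitness, not adenomas.

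Finally, the endpoint is secondary and descriptive. No test or sample size depends on it, and the Discussion ties a larger trial to NOTUM expansion and tolerability. This stands and limits the severity.

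**Conclusion.** The point holds, at moderate severity. The defined endpoint covers 18 months of which 6 are on drug, and a change of the form 2u + t cannot identify the lithium effect that the objective asks for. That conclusion needs only the timeline and the reading of end of study as month 18.

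The size of the dilution is conditional. Reductions of 25%, 50% and 100% shrink to 8%, 17% and 33% under constant untreated growth, an immediate effect and no rebound. Full rebound gives 0%. An effect delayed past month 12 would be missed by months 6–12 against 0–6.

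It would be too strong to call this a flaw that threatens the trial. The primary outcome is unaffected, and the adenoma result is descriptive in 12 patients. Nor would the redefined contrast give a clean causal estimate: every patient has the same sequence in a single arm, so drug and time remain partly confounded.

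**What to change.** Redefine the secondary adenoma endpoint as within-patient change in adenoma number and in sum of diameters, by period:

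1. Month 6–12 (on lithium) against month 0–6 (untreated), as the main contrast.
2. Month 12–18 reported separately as the off-treatment period, where a delayed effect or rebound would show.
3. Baseline to month 18 kept as a descriptive summary only.

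For every interval, measure from the burden left after excision at its start to the burden before excision at its end. This needs the number and diameter of lesions removed at each colonoscopy. Table 1 alone will not give this, because the 5 mm excision threshold falls inside its 3–5 mm column. State in the report that the fixed sequence leaves drug and time partly confounded.

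Cost: a change of wording before analysis, plus recording excised lesions and accounting for them in the calculation. All four colonoscopies and video reads are already planned, so no visits or procedures are added.
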